### Procedures for assessing invasive coronary physiology indices

Using specialised intracoronary wires (ComboWire) simultaneous measurements of coronary perfusion pressure and blood flow velocity will be performed that will provide specific coronary physiological data in addition to ^13^N-ammonia PET-determined CFR. With these high-fidelity measurements, we can estimate coronary flow, the components of the coronary wave profile and indices of microvascular function. During the invasive study, this wire will be placed in the distal coronary artery, and simultaneous measurements of aortic pressure, distal coronary pressure and distal coronary blood velocity will be performed during rest conditions and following adenosine (140 mg/kg/minute)-induced hyperaemia.

At the end of each study, data will be exported onto CD-ROMs, and appropriate cardiac cycles will be selected using custom-made software (Study Manager; Volcano Corp.). These selected beats will be analysed in another custom-made software application (Cardiac Waves, written in MATLAB, Delphi version 2010; Embarcadero Technologies, San Francisco, CA, USA). The flow and pressure data for the selected cardiac cycles are ensemble-averaged, which filters out background noise and allows identification and exclusion of non-physiological recordings. These provide means of average peak velocity (APV; the average of three to five instantaneous peak coronary flow velocities), aortic and distal coronary pressures, and wave intensity analysis (WIA) at each time point. These parameters will be used in calculations to determine the following indices:
*CFR*: We will assess APV at rest and following adenosine stress in the vessel that has undergone PCI. We can then determine vessel-specific regional CFR using the formula CFR = APV_stress_/APV_rest_.
*WIA*: This is a time-domain method of depicting a waveform in terms of a succession of multiple small wavefronts. WIA is invaluable in understanding the forces driving coronary flow, and a key element of this, the BEW, has been implicated in a number of disease processes [18]. We will assess WIA during conditions of adenosine-induced hyperaemia in all three vessels. We expect that there will be increased dominance of the BEW with CXCR2 therapy as compared with placebo.
*Microvascular resistance*: This is the ratio between distal coronary arterial pressure (P_d_) and coronary flow. The hyperaemic microvascular resistance (hMR) is a velocity-based index of microvascular resistance and is the ratio of P_d_ to APV during maximal hyperaemia. It is calculated using the formula hMR = P_d_/APV. Microvascular resistance is expected to be reduced after 24 weeks of treatment with CXCR2 inhibition as compared with placebo.

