### Participant timeline

If eligible, subjects are scheduled for the following study visits (Fig. 1). Patients undergo invasive coronary angiography with PCI as per normal clinical care, but they will also undergo IVUS to provide greyscale and virtual histology of all major coronary arteries. Patients with suitable coronary anatomy will be invited to have invasive assessment of coronary and microvascular physiology under adenosine-induced hyperaemia (using a ComboWire; Volcano Corp., Rancho Cordova, CA, USA).

Four weeks later, subjects will re-attend the cardiology department, at which time a full history and physical examination will be performed and inclusion criteria confirmed. Assessments will include a 12-lead electrocardiogram, as well as blood tests (fasted) for blood count and biochemistry (renal, liver, lipid, glycaemic and thyroid profiles) and high-sensitivity C-reactive protein (hs-CRP) and homocysteine levels. Screening blood tests for disorders which may exclude patients from the study will be drawn as indicated (e.g., serum hepatitis B surface antigen, hepatitis C antibody, and HIV testing if prompted by history). Additionally, an aliquot of blood will be taken for measurement of circulating monocyte-platelet aggregates (MPAs, a highly sensitive and reproducible index of degree of platelet activation) by flow cytometry. In the case of women of childbearing potential, pregnancy will be excluded by performing a pregnancy test on a spot urine. Once eligibility has been confirmed, ^13^N-ammonia PET-CT cardiac scans will be obtained at rest and during adenosine-induced hyperaemia to measure CFR. The CT scan will be obtained prior to the PET scan for attenuation correction at rest and stress, and prior to the rest scan, the CT scan will also be used to measure calcium score.

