After randomisation, subjects will be allocated 2:1 to receive either AZD5069 or matched placebo, orally, for the succeeding 24 weeks. At different time points (weeks 1, 2, 4, 8, 12, 16, 20 and 24), patients will attend for repeat visits, at which time they will undergo a physical examination and have a blood sample taken for the purpose of determining safety and efficacy biomarkers. At weeks 1, 12 and 24, patients will attend prior to their morning dose, and additional blood samples will be taken for the purpose of measuring plasma drug levels. At weeks 4, 8, 12, 16, 20 and 24, spot urine samples will be obtained from women of childbearing potential in order to exclude pregnancy; if they have a positive test result at any point, they will be immediately withdrawn from the study. At week 24, a repeat ^13^N-ammonia PET scan will be obtained to assess change from baseline in total CFR, and at the same time point, repeat coronary angiography together with IVUS will be performed to assess change in plaque composition and degree of restenosis. Those patients who initially had a ComboWire assessment will be invited to have a repeat assessment at the time of their repeat coronary angiography. A flow diagram of the protocol is shown in Fig. 2.

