### Outcome measurements

The primary outcome is the change in total CFR from baseline, as measured by ^13^N-ammonia PET, before and after 24 weeks of treatment with AZD5069 or matched placebo. The secondary endpoints are as follows:Change in plaque composition, as measured by VH-IVUS, before and after 24 weeks of treatment with AZD5069 or matched placeboDegree of in-stent restenosis, as measured by IVUS, before and after 24 weeks of treatment with AZD5069 or matched placeboChange in the magnitude of the backward expansion wave (BEW), as measured by ComboWire assessment, before and after 24 weeks of treatment with AZD5069 or matched placebo

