### Procedures for assessing coronary flow reserve with PET

#### Image acquisition

Patients will be asked to abstain from methylxanthine derivatives, including caffeine, for ≥ 24 h before ^13^N-ammonia PET scan acquisition. Vasodilator medications such as nitrate, β-blockers or calcium channel blockers will be stopped 24 h before PET scan acquisition.

PET imaging will be performed using a Discovery 710 PET-CT scanner (GE Healthcare, Waukesha, WI, USA). An intravenous bolus injection of 550 MBq of ^13^N-ammonia will be given for both stress and rest image acquisition. A total of 47 transaxial slices will be reconstructed over an axial FOV of 15 cm. The acquired PET pixel size is 2.73 × 2.73 × 3.27 mm. A CT scout projection determines the heart position within the patient, and low-dose cine CT (100 kV, 10 mA, 0.5 second/rotation, 40-mm collimation, 5.5-second duration) will be used for attenuation correction of PET data. The PET acquisition consists of a series of dynamic scans from 0 to 6 minutes (12 × 10 seconds, 6 × 20 seconds and 2 × 60 seconds) followed by a single 20-minute gated static scan. Approximately 30 minutes after completion of rest imaging, stress imaging will be performed with adenosine (140 μg/kg/minute) infused intravenously for at least 3 minutes before tracer injection. CT-based attenuation correction will be repeated for the stress study.

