### Procedures for assessing coronary restenosis and plaque composition

#### Image acquisition

Angiography and IVUS imaging will be performed after administration of 200 μg of intracoronary nitroglycerine. Angiography will be performed so that each vessel is viewed from at least two orthogonal angles after the planned PCI. For the IVUS procedure, a 45-MHz, 3.2-French, rotational IVUS catheter (Revolution; Volcano Corp.) will be used. After the IVUS catheter is placed in the distal vessel, the catheter will be pulled back to the aortic ostium using the motorised pull-back system at 0.5 cm/second. During pull-back, greyscale IVUS will be recorded and displayed in real time, and raw radiofrequency data will be captured at the top of the R wave for post-procedural reconstruction of the colour-coded map by a VH-IVUS data recorder (s5 Imaging System; Volcano Corp.).

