A secondary outcome is the change in the magnitude of the BEW, a key component of the coronary wave profile, with maximal hyperaemia. From previous work, we expect the magnitude of the BEW to increase 40% with adenosine induced maximal hyperaemia in patients with CAD. Unpublished data from the host centre suggest that in patients without CAD, the BEW can increase a further 14%. Assuming an α error probability of 0.05 (two-tailed), power 0.80 and allocation ratio 2:1 (active drug to placebo), power calculation (using G*Power 3.1.3 software) indicates that we would need 26 subjects in the active and 13 subjects in the placebo group. The BEW measurement has a standard deviation of 21%, as such we will need to recruit 57 patients in total to undergo ComboWire assessment as part of their invasive protocol.

A full description of the statistical analysis plan is beyond the scope of this protocol, and will be published separately. In summary, the primary analysis will be an intention to treat analysis. An analysis of covariance model will be used to obtain an estimate for the mean difference in total CFR between the two treatment groups including covariates for baseline CFR. The estimated treatment effect will be reported with 95% confidence intervals and corresponding *p* value.

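### The adenosine rate for the invasive ComboWire study is printed in mg instead of μg, 1000 times the rate given for PET stress

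*Protocol article*

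**What the plan says.** The Protocol article uses adenosine to induce hyperaemia in two procedures and gives a rate for each.

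- **PET stress scan** (Procedures for assessing coronary flow reserve with PET, Image acquisition): "stress imaging will be performed with adenosine (140 μg/kg/minute) infused intravenously for at least 3 minutes before tracer injection".
- **Invasive ComboWire study** (Procedures for assessing invasive coronary physiology indices): pressure and flow velocity are recorded at rest and "following adenosine (140 mg/kg/minute)-induced hyperaemia".

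The invasive procedure is optional. Under Participant timeline, "Patients with suitable coronary anatomy will be invited to have invasive assessment of coronary and microvascular physiology under adenosine-induced hyperaemia", and at week 24 "Those patients who initially had a ComboWire assessment will be invited to have a repeat assessment". It supplies a secondary endpoint, the change in the "magnitude of the backward expansion wave (BEW), as measured by ComboWire assessment" (Outcome measurements). The planned number is in Statistics and sample size calculation: "we will need to recruit 57 patients in total to undergo ComboWire assessment".

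**The concern.** The two rates share the drug, the number 140, the per-kg-per-minute form and the aim of hyperaemia. They differ only in the mass unit, and the article gives no reason for a different dose in the catheter laboratory. Read literally, the invasive rate would be dangerous.

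This is a value stated wrongly, so it is not a detail that a condensed article may leave to the full protocol. It is also the only rate given for the invasive study. Participant timeline and Statistics and sample size calculation both mention adenosine hyperaemia there without a dose. To find the right figure, a reader must turn to the PET section and assume that the same rate applies.

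Two things are at stake. The first is a correct description of the stimulus under which the BEW is measured; the invasive coronary flow reserve and the hyperaemic microvascular resistance rest on the same stimulus. The second is patient safety, but only if the mg unit was copied from, or into, the documents that staff use at the bedside.

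**Working it through.** **Inputs from the article**

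| Item | PET stress | Invasive ComboWire study |
|---|---|---|
| Drug | adenosine | adenosine |
| Purpose | hyperaemia | hyperaemia |
| Printed rate | 140 μg/kg/minute | 140 mg/kg/minute |
| Route | intravenous | not stated |
| Duration | at least 3 minutes before tracer | not stated |

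**Step 1: ratio of the printed rates.** 140 mg/kg/minute = 140 × 1000 = 140,000 μg/kg/minute. 140,000 / 140 = 1000 exactly.

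**Step 2: what each rate would deliver.** Dose per minute = rate × body weight. The article gives no weight, so the weights below are assumptions.

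| Assumed weight | As printed (140 mg/kg/minute) | With the PET unit (0.140 mg/kg/minute) |
|---|---|---|
| 50 kg | 140 × 50 = 7,000 mg/minute = 7 g/minute | 0.140 × 50 = 7 mg/minute |
| 70 kg | 140 × 70 = 9,800 mg/minute = 9.8 g/minute | 0.140 × 70 = 9.8 mg/minute |
| 100 kg | 140 × 100 = 14,000 mg/minute = 14 g/minute | 0.140 × 100 = 14 mg/minute |

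**Step 3: could the text reading have lost the μ sign?** The sign is intact for the same drug in the PET section. It is also intact in the section on restenosis and plaque composition, where imaging is done "after administration of 200 μg of intracoronary nitroglycerine". A general loss of the symbol is therefore unlikely. A fault in one character cannot be excluded.

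**Step 4: how many patients the procedure concerns.** The ComboWire recruitment target is 57 and the trial size is 90, so 57/90 = 63.3%. The week-24 repeat is by invitation, so 57 is an upper bound on the target at that visit.

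**Step 5: effect on other figures.** Adenosine dose enters neither the power calculation for the primary outcome nor that for the BEW. The PET rate is already printed in μg. No sample size, power or analysis figure changes.

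**The case against.** Nobody can reasonably dispute the contradiction itself. The case on the other side concerns its weight.

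- **It may be purely editorial.** If the article alone carries the slip, no result is affected, and the safety point depends on documents that are not shown. Clinical staff would very likely recognise the figure as impossible. All of this stands, and it rules out a critical rating. It does not make the correction optional, because the wrong value is the only stated dose for a procedure carried out on trial patients.
- **Symbols are not handled uniformly in this text.** The multiplication sign is present in the neutrophil threshold under Inclusion and exclusion criteria and missing from the one under Withdrawal of subjects. This weakens the argument that μ is intact elsewhere. A dropped sign is not the same fault as one letter replaced by another, however, and the doubt is met by checking the approved protocol before anything is corrected.
- **The figures illustrate and do not measure exposure.** The g/minute values rest on assumed weights, and nothing suggests that anyone received such a dose. The 63% is also only a guide: the baseline ComboWire study takes place at the PCI, four weeks before eligibility is confirmed, so some patients could undergo it without being among the 90 randomised. The BEW power calculation itself asks for 26 + 13 = 39 patients, and 57 is the recruitment figure stated after it. These caveats stand. The factor of 1000 depends on none of them.
- **Worksheets are outside the article.** Nothing in it shows that they carry the wrong unit. That is true, but recruitment is described as ongoing, and a check costs very little against the harm if the unit had been copied.

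**Conclusion.** The concern holds. The invasive adenosine rate is wrong as printed or, at the least, contradicts the PET rate by a factor of exactly 1000, and a slip of mg for μg is by far the most likely explanation. It should be fixed.

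The conclusion assumes that both procedures were meant to use the same rate, which the identical numeral, form and purpose support, and that the mg is in the published text and did not arise when the file was read.

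Its reach is limited. The primary PET outcome, sample size, power and analysis model are untouched. If the slip is confined to the article, the BEW comparison is untouched too. There is no evidence that any patient was given a wrong dose.

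**What to change.** 1. Check the rate for the ComboWire study in the approved full protocol.
2. If it reads μg there, publish a correction so that the section on invasive coronary physiology indices gives adenosine at 140 μg/kg/minute, in line with the PET section.
3. Check that the catheter-laboratory worksheets carry the μg unit. If the full protocol or any worksheet has mg, correct it at once.

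The cost is one unit in the text and a short check of site documents. Design, sample size and analysis stay as they are.

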### Laboratory measurements

A full blood count will be performed by the haematology laboratory at St. Thomas’ Hospital. Blood (2 ml) will be sent in an ethylenediaminetetraacetic acid (EDTA) vacutainer tube to the laboratory within 30 minutes of venesection. Blood biochemistry (renal, liver, lipid, glycaemic and thyroid profiles), hs-CRP and homocysteine assays will be performed by the biochemistry laboratory at St. Thomas’ Hospital. Blood (10 ml) will be sent in a clotted vacutainer tube to the laboratory within 30 minutes of venesection.

Circulating MPA measurement will be performed in our research laboratories by flow cytometric analysis of whole blood (4 ml) collected in sodium citrate (0.3% final concentration). Immediately after venepuncture, blood will be immunostained with different combinations of peridinin–chlorophyll-protein complex-conjugated anti-human CD14, fluorescein isothiocyanate-conjugated anti-human CD16 and allophycocyanin-conjugated anti-human CD42b or CD62P. Isotype control antibodies will be used as negative controls. After red cell lysis using fluorescence-activated cell sorting lysing solution (BD Biosciences, San Jose, CA, USA), samples will be fixed in 1% paraformaldehyde and kept at 4 °C until analysed within 48 h by flow cytometry.

At visits 4, 8 and 11, we will measure pre-dose (trough) and peak (2 h post-dose) AZD5069 plasma concentrations in all subjects. Pharmacokinetic assays of AZD5069 and its major human metabolite AZ13587715 will be conducted via a contracted vendor (Covance Inc., Princeton, NJ, USA) that has created and validated the LC/MS-based analytical method for assessment of AZD5069 and AZ13587715 in human plasma preserved in EDTA and stored between − 10 °C and − 30 °C. The analytical method will be identical to that used in prior human studies of AZD5069 [13, 19–21]. At monthly intervals, spot urine samples will be obtained from women of childbearing potential in order to exclude pregnancy (Alere hCG Easy; Alere Inc., Waltham, MA, USA).

### Emergency code break

A 24-h emergency code break and medical information will be provided by ESMS. Each randomised subject will be provided with a card detailing code break telephone numbers and emergency contact details. Subjects will be requested to carry this card with them always whilst participating in the trial.

### Withdrawal of subjects

The study drug must be discontinued if any of the following occur:An exclusion criterion is incident during the study.Absolute neutrophil count < 1 10^9^/L is noted in two consecutive samples within 48 h.The participant misses > 20% of his or her doses.The participant decides he or she no longer wishes to continue.It is recommended by the investigator.

Participants have the right to withdraw from the study at any time for any reason. The investigator also has the right to withdraw patients from the study drug in the event of inter-current illness, adverse events (AEs), serious adverse events (SAEs), suspected unexpected serious adverse reactions (SUSARs), protocol violations, cure, or administrative or other reasons. It is understood by all concerned that an excessive rate of withdrawals can render the study un-interpretable; therefore, unnecessary withdrawal of patients should be avoided. Should a patient decide to withdraw from the study, all efforts will be made to report the reason for withdrawal as thoroughly as possible. Should a patient withdraw from study drug only, efforts will be made to continue to obtain follow-up data with the permission of the patient. Participants who wish to withdraw from trial medication will be asked to confirm whether they are still willing to provide the following:Trial-specific data at subsequent scheduled visitsClinical follow-up data collected as per routine clinical practice

### Reporting procedure for all adverse events

Information on all AEs, serious and non-serious, is collected, documented and reported on the appropriate eCRFs/SAE reporting forms once informed consent has been signed, and this will end 14 days after completing the study medication. The following information is recorded:Participant detailsAE descriptionBody system codeStart date of eventEnd date of eventOutcome of eventIntensity/severity of eventStudy procedure related (i.e., causality/relatedness)Investigational Medical Product (IMP) related (i.e., causality/relatedness)Whether the event is seriousFollow-up information recorded as necessary

AEs considered to be related to study procedure or medication as judged by a medically qualified investigator are followed until resolution or the event is considered stable. All related AEs that result in a subject’s withdrawal from the study or present at the end of the study are followed until a satisfactory resolution occurs.

### Reporting procedure for serious adverse events

King’s Health Partners Clinical Trials Office (KHP-CTO) will have responsibility for pharmacovigilance. All SAEs, SARs and SUSARs will be reported immediately by the chief investigator (and certainly no later than 24 h) to the KHP-CTO in accordance with the current pharmacovigilance policy. The chief investigator will report SUSARs to the ethics committee.

### Statistics and sample size calculation

Because the trial is randomised and double-blinded, all blood assays, ^13^N-ammonia PET scans and invasive coronary assessments will be performed with no knowledge of subject treatment allocation (AZD5069 or placebo). The primary outcome is change in total CFR as measured by ^13^N-ammonia PET. Formal power calculations are problematic because no data exist to date in humans on the relationship between CXCR2 inhibition and CFR. However, assuming a medium to large effect size (*d* = 0.7), α error probability of 0.05 (two-tailed), power 0.80 and allocation ratio 2:1 (active drug to placebo), power calculation (using G*Power 3.1.3 software) indicates that we would need 51 subjects in the active and 25 subjects in the placebo group.

Furthermore, unpublished observational data from AstraZeneca and the Göteborg Hospital (Göteborg, Sweden) which relate neutrophil counts in stable CAD and after myocardial infarction with echocardiographic CFR are shown in Table 1. On the basis of these analyses, we will recruit 60 into the active group and 30 into the placebo group, firstly to allow for lesser effect sizes and secondly to allow us to better stratify responses to CXCR2 inhibition on the basis of plasma IMP levels achieved.

**Table 1 Tab1:** Relationship between neutrophil count and coronary flow reserve based on previous studies

Study	Neutrophil count	Echo-based CFR (mean ± SE)	CFR increase	SD of PET-MPR [22]	Patients required (*p* < 0.05, 80% power)
Stable CAD cohort					
	5.8	2.10 ± 0.19		0.36	
	4.6	2.35 ± 0.12	10.6%	0.36	33
	4.2	2.43 ± 0.11	13.5%	0.36	19
Post-MI cohort					
	5.8	2.45 ± 0.07		0.36	
	4.6	2.64 ± 0.05	7.2%	0.36	57
	4.2	2.70 ± 0.05	9.3%	0.36	33

*Abbreviations: CFR* Coronary flow reserve, *PET* Positron emission tomography, *MPR* Myocardial perfusion reserve, *CAD* Coronary artery disease, *MI* Myocardial infarction

The relationship between neutrophil count and echo-based CFR in both stable CAD and post-MI cohorts is shown. This demonstrates that lower neutrophil counts are associated with higher CFR

A secondary outcome is the change in the magnitude of the BEW, a key component of the coronary wave profile, with maximal hyperaemia. From previous work, we expect the magnitude of the BEW to increase 40% with adenosine induced maximal hyperaemia in patients with CAD. Unpublished data from the host centre suggest that in patients without CAD, the BEW can increase a further 14%. Assuming an α error probability of 0.05 (two-tailed), power 0.80 and allocation ratio 2:1 (active drug to placebo), power calculation (using G*Power 3.1.3 software) indicates that we would need 26 subjects in the active and 13 subjects in the placebo group. The BEW measurement has a standard deviation of 21%, as such we will need to recruit 57 patients in total to undergo ComboWire assessment as part of their invasive protocol.

A full description of the statistical analysis plan is beyond the scope of this protocol, and will be published separately. In summary, the primary analysis will be an intention to treat analysis. An analysis of covariance model will be used to obtain an estimate for the mean difference in total CFR between the two treatment groups including covariates for baseline CFR. The estimated treatment effect will be reported with 95% confidence intervals and corresponding *p* value.

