**Methods/Design:**

Ninety subjects with coronary artery disease undergoing percutaneous coronary intervention will be included in this investigator-driven, randomised, placebo-controlled, double-blind, phase IIa, single-centre study. Participants will be randomised to receive either AZD5069 (40 mg) administered orally twice daily or placebo for 24 weeks. Change in coronary flow reserve as determined by ^13^N-ammonia positron emission tomography-computed tomography will be the primary outcome. Change in the inflammatory component of coronary plaque structure and the backward expansion wave, an invasive coronary physiological measure of diastolic function, will be assessed as secondary outcomes.

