### Secondary objective

The secondary objectives of the study are to ascertain, in patients undergoing PCI for atherosclerotic coronary disease, if 24 weeks of CXCR2 inhibition therapy will result in a reduction in the inflammatory component of coronary plaque, a decrease in the degree of in-stent restenosis and improvements in coronary microvascular function compared with placebo.

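### The BEW sample size rests on an adenosine response and a CAD versus no-CAD contrast, not on the listed 24-week change, and its figures do not follow from its inputs

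*Protocol article*

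**What the plan says.** The protocol article describes the BEW endpoint in three places.

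- **Outcome measurements** lists the change in BEW magnitude, by ComboWire, from before to after 24 weeks of AZD5069 or placebo. It does not say whether BEW is taken at rest or under hyperaemia.
- **Procedures for assessing invasive coronary physiology indices** sets the condition and the vessels for wave intensity analysis (WIA), from which BEW is derived: "We will assess WIA during conditions of adenosine-induced hyperaemia in all three vessels".
- **Statistics and sample size calculation** says "A secondary outcome is the change in the magnitude of the BEW, a key component of the coronary wave profile, with maximal hyperaemia" and does not mention 24 weeks. Its planning inputs are "we expect the magnitude of the BEW to increase 40% with adenosine induced maximal hyperaemia in patients with CAD", and then "in patients without CAD, the BEW can increase a further 14" per cent. With two-sided alpha 0.05, power 0.80 and 2:1 allocation it arrives at 26 active and 13 placebo. It then adds "The BEW measurement has a standard deviation of 21" per cent and concludes that 57 patients in total are needed.

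A related labelling point: the Secondary objective section asks for "improvements in coronary microvascular function compared with placebo", whereas the abstract calls BEW "the backward expansion wave, an invasive coronary physiological measure of diastolic function". Hyperaemic microvascular resistance (hMR) is defined and given a direction ("Microvascular resistance is expected to be reduced after 24 weeks of treatment with CXCR2 inhibition") but is not a listed endpoint.

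**The concern.** A sample size supports an endpoint only if its effect and SD belong to that endpoint. Here the listed variable is a change over treatment time. The planning figures describe what adenosine does to BEW within one session, and how that response differs between people with and without CAD. No figure is given for how far BEW moves over 24 weeks on drug or placebo, and the document does not say which BEW quantity the 21% SD describes.

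Two things are at stake. First, hyperaemic BEW and the rest-to-hyperaemia percentage increase are different variables and can give different answers, and the text leaves both open. Second, readers will take the ComboWire subset as powered at 80% for the BEW endpoint, so a null result could be over-read as evidence of no effect.

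**Working it through.** **Method check on the primary outcome.** A two-sample t-test (noncentral t), 2:1, two-sided 0.05, d = 0.7 needs 50 + 25 for 80% power. The protocol's 51 + 25 gives 0.808. The method therefore reproduces the protocol's own primary calculation to within one patient.

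**BEW inputs**, all from the sample size section: difference 14%, SD 21%, two-sided 0.05, power 0.80, 2:1.

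**Percentage-point reading.** d = 14 / 21 = 0.667.
- Normal approximation: placebo n = (1.96 + 0.842)² × (1 + 1/2) / 0.667² = 26.5, so 27, with 54 active; total 81.
- Noncentral t: 56 + 28 = 84.
- Power at 26 + 13: 0.48. Power at 57 (taken as 38 + 19): 0.65.

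**What the stated figures correspond to.** 26 + 13 is the requirement for d = 1.0 (power 0.82). 57 gives 80% power at d = 0.80. Neither d is stated. Going from 39 to 57 would mean a loss of 1 − 39/57 = 32%, and no such allowance is stated.

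**Other readings of the 14%.**

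| Reading | d | Needed | Power at 26 + 13 | Power at 57 |
|---|---|---|---|---|
| 14 points | 0.667 | 56 + 28 | 0.48 | 0.65 |
| 14% of 140 = 19.6 points | 0.933 | 30 + 15 | 0.76 | 0.90 |
| 14% of 40 = 5.6 points | 0.267 | 334 + 167 | 0.12 | 0.15 |

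No reading yields 39 or 57.

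**Effect short of normalisation.** Required N scales as 1/d². Half the gap (7 points, d = 0.333) needs 214 + 107 = 321 patients, about four times 84. Power at 57 is 0.21.

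**Allowing for baseline (assumption).** The document gives no baseline to week-24 correlation ρ for BEW. If 21% is the SD of a single measurement, ANCOVA leaves a residual SD of 21 × √(1 − ρ²). For 14 points:
- ρ = 0.3: 50 + 25 = 75 needed; power at 57 is 0.69.
- ρ = 0.5: 42 + 21 = 63 needed; power at 57 is 0.77.
- ρ = 0.7: 30 + 15 = 45 needed; power at 57 is 0.90.

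The threshold for 57 follows from its detectable d of 0.801: √(1 − ρ²) = 0.667 / 0.801 = 0.832, so ρ ≈ 0.55. A simple change-score analysis has SD 21 × √(2(1 − ρ)) and needs 114, 84 or 51 patients at ρ = 0.3, 0.5 or 0.7.

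**The case against.** The best defence is that the three sections can be read together. Outcome measurements supplies the time frame, the procedures section supplies the condition, and the hyperaemia phrase in the sample size section repeats that condition. The endpoint is then the 24-week change in hyperaemic BEW. This is a fair reading of the definition, but it does not rescue the planning figures: 40% is still a rest-to-adenosine rise and 14% is still a contrast between patient groups.

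Three stronger conclusions might be inferred, and the document does not support them.

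- *That the power figure is right, but for the unlisted rest-to-hyperaemia response.* The numbers do not follow from 14% and 21% for either quantity.
- *That analysts could choose between PCI-vessel and all-vessel BEW, giving four analyses and, if independent, a 1 − 0.95⁴ = 19% false-positive risk.* Only invasive CFR is tied to the PCI vessel; WIA is assigned to all three vessels. How the three are combined can be left to the analysis plan, and a per-patient summary is consistent with counting patients. The two BEW definitions also overlap, so independence would not hold.
- *That the microvascular objective cannot be answered.* The three secondary objectives match the three secondary endpoints in order, so BEW appears to be the intended one. The Background also describes CFR, the primary outcome, as covering microvascular as well as macrovascular function. What remains is a mismatch of labels.

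It is also fair that BEW is a secondary measure in an invited subset of a phase IIa trial.

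**Conclusion.** The point holds as a mismatch between the listed BEW endpoint and the inputs used to size it, together with a calculation that does not reproduce. The 80% power claim is not established for the 24-week change. Taking 14% as percentage points, 21% as the SD of the analysed value and no baseline adjustment, about 84 patients are needed; 39 and 57 give roughly 48% and 65% power. Those figures already assume that 24 weeks of drug closes the whole gap between CAD and non-CAD responses.

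The size depends on assumptions that the document does not settle. Under ANCOVA, 57 patients would reach 80% power for 14 points if the baseline correlation were about 0.55 or higher. Reading 14% as a share of 140% would also make 57 sufficient, though not 39. So the finding is that the power is unsupported, not that 57 is certainly too few.

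**What to change.** 1. State one BEW variable identically in Outcome measurements, the invasive physiology procedures and the sample size section: either hyperaemic BEW or the rest-to-hyperaemia percentage increase. Define it as a per-patient value from the three vessels, compared between arms at week 24 by ANCOVA on its baseline value. Label the other form exploratory.
2. Restate the BEW power for that variable at the planned ComboWire number. Give the effect, its unit (points or relative), the SD of that same variable, any assumed baseline correlation and any allowance for loss. Reconcile 26 + 13 with 57.
3. Say that the 14% effect assumes full normalisation to a non-CAD response.
4. Optionally, name hMR as a supporting endpoint for the microvascular objective, since it is already measured and has a stated direction.

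The cost is wording only, with no new measurement: rest and hyperaemic recordings are already planned. One BEW form becomes exploratory, and the stated power will probably look less favourable unless a high baseline correlation can be justified.
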